**Methods:**

We will employ a mixed method study design which is divided into two phases. Phase 1, namely the qualitative elicitation research phase will inform the development of the quantitative intervention phase (phase 2), consisting of a cluster-randomized trial, based on input from key stakeholders. The study will be undertaken in 16 government-funded primary schools in the iLembe district of KwaZulu-Natal, South Africa. The study will target learners in Grades 4 and 7, their parents, Life Orientation educators, school principals and members of school governing bodies. Assessment for the primary objective (BMI Z scores), and the secondary objectives (change in knowledge, attitudes and behaviours regarding diet and physical activity) in both study arms will be conducted at baseline in March 2020 and at the end of the study in October 2020.

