Therefore, there is a need to develop and implement interventions that are specific for lifestyle diseases and conditions that target the child groups relevant to South Africa. Such interventions may be difficult to conduct and sustain due to a lack of funding and resources. Thus, the i-SPAN study has been developed and will be conducted in the poverty-challenged iLembe District in the province of KwaZulu-Natal in South Africa. The elicitation research phase will inform the development of an intervention phase that will design, implement and assess the effectiveness of school-based interventions that focus on diet and physical activity in children and adolescents in Grades 4 and 7 (aged 9–15 years). It is during these years that most girls (8–13 years) and boys (10–15 years) enter puberty, reaching a growth peak that results in a healthy BMI and weight [16].

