#### Phase two: intervention

4.To assess the effectiveness of the i-SPAN study in children and adolescents aged 9–15 years by comparing the intervention and control arms at baseline and at the end of the study regarding:
BMI Z scores.Proportion of children and adolescents classified as overweight and obese.Knowledge, attitude and behaviours regarding diet and physical activity.5.To describe and evaluate the outcomes of the interventions for scientific dissemination.

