Anthropometry	Weight and height for all participating children and adolescents	Phase 2- Intervention phase	Weight and height will be measured using a digital weighing scale, and stadiometers. (Model no. 210/217/876; Seca, Hamburg, Germany). The weight of the participant will be taken to the nearest 0.1 kg for accuracy. The participants will be weighed with minimal clothing, and preferably with an empty bladder and before a meal [26]. Measurements using the stadiometer will be taken to the nearest 0.1 cm for accuracy. The participants will be measured without shoes. Participants are required to stand with their legs straight, heels and the height measure touching at the back, arms at the sides, relaxed shoulders, with chin level to ground and looking straight ahead [26]. Weight and height measurements will be taken in duplicate for accuracy and a correct average. The body mass index (BMI) for age Z scores, according to the 2006 WHO Growth Standards for children, will be used to classify being at risk of overweight with a Z score of SD 1, overweight with a Z score SD > 1 and obese as a Z score SD > 2 [27].
Workshop	LO educators	Phase 2- Intervention phase	To facilitate study implementation, educators will be invited to attend a two-day training workshop at the university to assist educators in understanding and delivering the classroom lessons as part of the intervention. They will also be provided with the findings of the baseline data to assist them.

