### Planned statistical analysis

#### Descriptive and analytical statistics

The use of weight and height, BMI calculations, completed questionnaires, arising from the interventions will use both descriptive and inferential statistics to analyse the data. To ensure succession of cluster randomization, the presence of any significant differences between the control and intervention cluster for the baseline characteristics of the participants such as sex, age, etc., will be examined using bivariate mixed effect regressions to account sufficiently for the clustered design. Data will be processed and analysed using Stata 13.0 SE. Mixed effects using generalized linear and logistic modelling approaches will be used to compare continuous and binary endpoints respectively among students in schools in intervention and control arms of the study. A within school random effect will be incorporated to account for correlated (repeated) measurements within each school to correctly estimate the significance when comparing pre- and post-intervention periods. Outcome variables include change in BMI at baseline and end of study, dietary intake, time spent in sedentary behaviours, diet and physical activity self-perception and practices, including overall knowledge and attitude regarding diet and physical activity- significant levels and stratified analyses.

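### The primary objective is BMI Z score, but the analysis section names change in BMI, so the scale of the primary analysis is contradictory

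*Protocol article*

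**What the plan says.** The Methods part of the Abstract reads "Assessment for the primary objective (BMI Z scores), and the secondary objectives". Objective 4, under Phase two: intervention, compares the arms at baseline and end of study, and its first two items are "BMI Z scores.Proportion of children and adolescents classified as overweight and obese".

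The Anthropometry row of Table 1 mentions Z scores once, to assign weight status: "The body mass index (BMI) for age Z scores, according to the 2006 WHO Growth Standards for children, will be used to classify".

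The section Descriptive and analytical statistics is the only quantitative analysis section. It opens with weight, height and BMI calculations, and then states:
- the outcomes: "Outcome variables include change in BMI at baseline and end of study, dietary intake, time spent in sedentary behaviours";
- the models: "Mixed effects using generalized linear and logistic modelling approaches will be used to compare continuous and binary endpoints respectively";
- the handling of repeated measurement, for comparing the periods before and after the intervention: "A within school random effect will be incorporated to account for correlated (repeated) measurements within each school";
- a check on randomisation, examining "the presence of any significant differences between the control and intervention cluster for the baseline characteristics of the participants".

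The words Z score do not occur in that section.

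**The concern.** The variable named as primary is not the variable named for analysis. BMI for age is standardised for the child's age and sex, and BMI is not. The trial spans two grades and ages 9–15, with about seven months between measurements (March to October 2020). The Background says of these years that "most girls (8–13 years) and boys (10–15 years) enter puberty, reaching a growth peak". Over such an interval a change in BMI and a change in BMI Z need not agree in size or in precision. With both left open, the scale could be settled after the results are known.

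A secondary question is how the baseline value is used. A change score is one option and adjustment for baseline is another, and they differ in precision. A third, smaller matter is the plan to test baseline differences for significance as evidence that randomisation worked.

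**Working it through.** **1. Outcome scale: the places side by side**

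| Place | Continuous weight outcome |
|---|---|
| Abstract, Methods | BMI Z score, named as primary |
| Objective 4 | BMI Z score, listed first |
| Table 1, Anthropometry | BMI-for-age Z score, used to classify weight status |
| Descriptive and analytical statistics | change in BMI; no Z score |

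Two readings are possible. Either change in BMI is shorthand for change in BMI Z, or Z scores serve only to classify children and BMI is the continuous outcome. Table 1 and the mention of BMI calculations fit the second reading. The Abstract and objective 4 fit the first. Nothing in the article settles it.

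**2. Change score against baseline adjustment**

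Take unit variance at each time and let r be the baseline/follow-up correlation. The article gives no r, so a range is assumed.

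- Change score variance: 2(1 − r)
- Baseline-adjusted variance: 1 − r²
- Difference: 2(1 − r) − (1 − r²) = (1 − r)², which is never negative

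| Assumed r | Change | Adjusted |
|---|---|---|
| 0.5 | 2 × 0.5 = 1.00 | 1 − 0.25 = 0.75 |
| 0.7 | 2 × 0.3 = 0.60 | 1 − 0.49 = 0.51 |
| 0.9 | 2 × 0.1 = 0.20 | 1 − 0.81 = 0.19 |

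**3. The same comparison on the power scale**

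Inputs from Sample size/power calculation: 8 schools per arm, 68 children per school, standardised difference 0.3, ICC 0.05, two-sided 5%.

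- Design effect: 1 + 67 × 0.05 = 4.35
- Children per arm: 8 × 68 = 544
- Effective number per arm: 544 / 4.35 = 125.06

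Without any use of baseline, these inputs give 66.0% power (normal approximation) or 59.8% (t, 14 df). They do not reproduce the stated 90%. That is a separate matter, and the inputs serve here only to scale the comparison.

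Multiplying the variance by the factors above, with r taken as equal at child and school level:

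| Assumed r | Change score, normal (t, 14 df) | Adjusted, normal (t, 13 df) |
|---|---|---|
| 0.5 | 66% (60%) | 78% (72%) |
| 0.7 | 87% (81%) | 91% (87%) |
| 0.9 | above 99% for both | above 99% for both |

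These figures leave sub-district out of the model.

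**4. Chance imbalance at baseline**

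Suppose the arms differ by g at baseline by chance. With no intervention effect, the expected follow-up gap is r·g. A change score subtracts g, leaving (r − 1)g: −0.1g at r = 0.9 and −0.5g at r = 0.5. So it over-corrects, slightly when r is high. Baseline adjustment subtracts r·g.

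**The case against.** The analysis section never says raw or unstandardised BMI. Its list of outcomes opens with a word that makes it non-exhaustive, and Table 1 does define BMI for age. A reader might infer that the trial will report a different primary variable from the one it set out. The text does not support that; it supports only that the scale is contradictory. This limits the claim but does not remove it, because the one section that should name the primary variable names another.

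A reader might also infer that the balance tests stand in for baseline adjustment, or that chance imbalance goes uncorrected. Neither holds. The tests are offered as a check on randomisation, and the baseline value enters through the change outcome and the pre/post model. That no baseline covariate is named is not in itself a fault, since a condensed article may leave the covariate list to the full analysis plan.

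The growth argument can be pushed too far as well. Both grades are recruited in every school and the arms run concurrently, so normal growth is expected in both. It adds variability and makes BMI change harder to interpret, but it does not systematically bias the comparison.

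Finally, one could count false alarms: ten independent tests at 5% give 1 − 0.95^10 = 40%. The article names only sex and age before trailing off, and gives neither a number of tests nor grounds for independence. It ties no action to a significant result, so the tests do not alter the treatment estimate. The 40% should carry no weight.

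**Conclusion.** The contradiction over the primary variable stands on the article's own words and carries this point. It needs resolving whichever reading was intended: a small wording correction if BMI Z was meant, a substantive decision if it was not.

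Baseline adjustment is a free improvement over the change score rather than the repair of an error. Its size depends wholly on an r that the article does not give. If BMI tracks closely over seven months, with r near 0.9, the gain is about 5% of the variance (0.19 / 0.20 = 0.95). For questionnaire scores, if r is nearer 0.5, it is 25% (0.75 / 1.00). The variance formulas assume equal variances at the two times, and the power figures also assume the same r at child and school level.

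The baseline significance tests are a minor matter. Under proper randomisation any baseline difference is due to chance, so a test cannot show that randomisation succeeded, but nothing in the plan depends on the outcome of the test.

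**What to change.** In Descriptive and analytical statistics, state one primary analysis: end-of-study BMI Z score compared between arms in the planned mixed model with a school random effect, adjusted for baseline BMI Z and for sub-district. Sub-district belongs in the model because Participants and recruitment process allocates two schools to each arm within each of the four sub-districts. Delete change in BMI or label it supportive. The same form suits the questionnaire scores, and a logistic version suits the overweight and obese proportion.

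Replace the significance tests of baseline characteristics with a descriptive table by arm.

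The cost is wording only. Weight and height are already planned at both times, and no further data are needed. The choice of scale should be recorded before anyone sees outcome data by arm.

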#### Qualitative analysis

All transcribed data from the FGDs and in-depth interviews will be managed using NVIVO8. The data will be imported to the NVIVO8 program, linked to memos where coding will occur. Topics and concepts will be coded i.e. to capture information about happenings, ideas or specific topics, and nodes will be created to mark relevant information to be analysed or searched [35]. Thereafter, data will be manually analysed for emerging common themes.

## Discussion

To our knowledge, this is the only other RCT to be conducted in South Africa, and the first in KwaZulu-Natal, that includes diet and physical activity school-based interventions. To encourage behaviour change and management of malnutrition nutrition, education (that includes diet and physical activity) is an important strategy that must be considered [36]. Nutrition education extends beyond the dissemination of food information; it includes addressing the needs of children and adolescents, parents and the community, empowers and encourages decision-making and choice of foods, encourages change in attitudes, beliefs and influences based on resources available and the needs of individuals, as well as improving and promoting the nutrition knowledge within cultural boundaries [37, 38]. Nutrition education serves to not only impart important nutrition information and health messages but rather involves the participants to engage in activities and/or interventions that will improve nutrition [39]. If the i-SPAN study is effective, this RCT will be implemented to other schools, including the study control schools in iLembe district and outside of iLembe as part of the prevention and management of childhood obesity in KwaZulu-Natal.

## Data Availability

Not applicable.

## Abbreviations

BMI: Body mass index
BREC: Biomedical Research Ethics Committee
DoBE: Department of Basic Education
DoH: Department of Health
FGD: Focus group discussion
i-SPAN: iLembe School Physical Activity and Nutrition
LO: Life Orientation
NCDs: Non-communicable diseases
PPS: Probability proportional to size
RCT: randomized controlled trial
SCT: Social Cognitive Theory
SPIRIT: Standard Protocol Items: Recommendations for Interventional Trials
UKZN: University of KwaZulu-Natal
WHO: World Health Organization
